### Analysis

Analysis of stepped wedge designs is challenging [54]. The unidirectional aspect of stepped wedged trials complicates analysis because the treatment effect cannot be estimated exclusively from within-cluster comparisons [59]. Analytical techniques depend on a number of factors including: the existence of a temporal effect on the outcome, equality or inequality in cluster size, and normality of continuous data. Based on a design using equal cluster sizes, and assuming that there will be a temporal effect, linear mixed models (LMM) will be used [65]. If there are no temporal effects, then within-cluster analysis can be used to estimate the treatment effect. Random effects will be used to model correlation between individuals within the same cluster and measure the variance of individuals in a cluster and variance at the cluster-level [59]. Hussey et al. (2007) provide equations and worked examples for calculating both the within-cluster and between-cluster calculations [59].

We conducted power analysis based on a sub-set of body weight data collected at baseline at four hospital wards. In their first week of admission, the prevalence of patients with (i) BMI greater than or equal to 20 who lost 2 or more kg, and (ii) BMI less than 20 who lost 1 kg or more, was measured as 26.7%. Using equations seven and eight [59], a coefficient of variation $\left(\frac{\tau }{\mu }=\frac{0.056}{0.267}\right)$of 0.21, with four groups of 20 patients measured over five time periods totalling 400 patients, a power of 80% would detect a reduction in the prevalence of weight loss from 26.7% to 6.5%, ie a 75% reduction. If a smaller effect size is selected, such as a reduction in prevalence from 26.7% to 16.5% (a 38% reduction), the power is reduced to 29%.

It is also possible to calculate the required sample size for an adequately (80%) powered study. To detect a smaller effect size (a 38% reduction in proportion of patients experiencing weight loss), the total sample size required is 1800 patients, comprising 90 patients in each of four groups measured across the five time periods. Alternatively, although not feasible for reasons defined above, if all 25 wards were included in the sample and 20 patients were included from each ward at each of five time periods, the resulting study comprising a total of 2,500 patients would have a power of 69% to detect a 38% reduction in proportion of patients experiencing weight loss.

All of the outcomes except for the Alberta Context Tool will be analysed according to the stepped wedge design, as these data are all collected at each of the five measurement time periods of the study. The Alberta Context Tool will be compared using an hierarchical (nested) ANOVA to account for variation within, and between, wards. Analysis will be conducted using Stata software.

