### Sampling

The primary outcome data will be collected on a sample of patients from only one ward per group due to resource constraints. Given that the median length of stay in the hospital is only 4–5 days, and our requirement is to collect weight data over at least a 1 week period, we will purposively sample a ward that is most likely to care for patients who have a length of stay in excess of 7 days. To further minimise the number of patients for whom a weight on admission is collected but who are discharged before 7 days, patients with Diagnostic Related Groups (DRGs) known to have longer than average length of stay will be targeted. The following patients will be excluded from body mass measurement: those undergoing palliation or expected to die within a month, those undergoing amputation or surgical removal of large tumours, those admitted directly to the intensive care unit or with stays in intensive care of more than 3 weeks. A total of 20 patients for each of four wards will be weighed on each of five measurement periods, resulting in a total sample size of 400. Whilst it was desirable to include either more wards or more patients per ward (see power calculations in Analysis) in the sample, resource constraints limited the final sample size available for analysis. Given the size of the wards (typically 20–24 patients each) it is anticipated that it may take repeated weekly visits over an entire month to reach a total sample of 20 patients with body weight measurements for each sampling period. Patients whose length of stay exceeds 14 days will be weighed at day 14 and day 21 to allow calculation of change in weight over the first, second and third weeks of their admission. The second and third week data will both be analysed separately.

Secondary outcomes and hospital process measures will only be collected from the records of patients included in the primary outcome sample, described above. Written consent to weigh patients will not be sought because it is routine practice and part of usual care in the hospital.

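### Beside a time-adjusted default, the plan permits a before-after analysis without time adjustment when no temporal effect is judged present, and gives no criterion for that judgement

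*Protocol article*

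**What the plan says.** The Analysis section of the protocol article lists what the choice of method depends on, including "the existence of a temporal effect on the outcome". The default follows: "assuming that there will be a temporal effect, linear mixed models (LMM) will be used". The next sentence opens a second route: "If there are no temporal effects, then within-cluster analysis can be used to estimate the treatment effect". The article does not say how absence of a temporal effect would be established, or by whom and when.

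The same paragraph cautions that "the treatment effect cannot be estimated exclusively from within-cluster comparisons". The Stepped wedge trial section counts adjustment for temporal trends among the strengths of the design. The closing paragraph of the Analysis section ties all outcomes except the Alberta Context Tool to the stepped wedge design, but it does not withdraw the second route. Nothing in the article makes time adjustment unconditional.

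**The concern.** Wards cross only from control to intervention, so exposure rises with calendar time in every ward. A within-ward comparison that ignores period is a before-after comparison. It is valid only if the outcome would have been flat over the rollout, and that has to be judged from the same small data set.

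If a real trend is missed, it is reported as an intervention effect, and with a smaller standard error than the adjusted analysis would give. A downward drift in weight loss is plausible: the rollout lasts about a year in one hospital, and the Setting section describes an earlier local nutrition project and wider interest in improvement. Protection against such drift is a main reason for using this design.

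**Working it through.** **Inputs from the protocol.** Sampling section: "The primary outcome data will be collected on a sample of patients from only one ward per group due to resource constraints", hence four wards. Analysis section: "with four groups of 20 patients measured over five time periods totalling 400 patients"; control prevalence 0.267; between-ward SD τ = 0.056. The exposure pattern is that of Table 1. Alpha is not stated; 0.05 two-sided is assumed.

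**1. Reproduce the stated power.** The stepped-wedge variance with fixed period effects and a random ward effect is

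Var = I·s²(s² + Tτ²) / [(IU − W)s² + (U² + ITU − TW − IV)τ²].

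- I = 4 wards, T = 5 periods, U = 10 treated cells.
- W = 0 + 1 + 4 + 9 + 16 = 30 (squared period totals); V = 16 + 9 + 4 + 1 = 30 (squared ward totals).
- s² = 0.267 × 0.733 / 20 = 0.009786; τ² = 0.003136.
- Numerator: 4 × 0.009786 × (0.009786 + 0.015680) = 0.000997.
- Denominator: 10 × 0.009786 + 30 × 0.003136 = 0.1919.
- Var = 0.00519, SE = 0.0721.

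For 26.7% to 6.5%: Φ(0.202/0.0721 − 1.96) = 80.0% (stated 80%). For 26.7% to 16.5%: Φ(0.102/0.0721 − 1.96) = 29.3% (stated 29%). The one-sided calculation does not reproduce these figures. The planned power therefore already rests on period adjustment.

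**2. Bias of the fallback under a linear trend.** A ward with k control periods has mean control time (k + 1)/2 and mean treated time (k + 6)/2. The difference is 2.5 periods for every k. A linear change of b per period therefore adds 2.5b to the within-ward estimate. Five periods span four intervals, so the bias is 2.5/4 = 62.5% of the total change: 5 points for an 8-point fall and 6.25 points for a 10-point fall.

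**3. Apparent precision of the fallback.** The within-ward sum of squares of exposure is 0.8 + 1.2 + 1.2 + 0.8 = 4, so SE = √(0.009786/4) = 0.0495. Nominal power for 26.7% to 16.5% would be Φ(0.102/0.0495 − 1.96) = 54%, against 29% with period. An 8-point fall gives a bias of about one fallback SE (0.05/0.0495).

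**4. Simulation with no treatment effect.** Binomial cells, 4 wards × 5 periods × 20 patients, prevalence 0.267, τ = 0.056, 20,000 trials per setting. Period is dropped when its 4-df joint F-test gives p ≥ 0.05. This test and the trends are assumptions.

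| Total linear fall, points | Period test detects | Period never in model | Test, then drop | Period always kept |
|---|---|---|---|---|
| 0 | 5.1% | 5.2% | 6.0% | 5.1% |
| 5 | 6.2% | 10.0% | 10.6% | 5.2% |
| 10 | 11.1% | 27.5% | 26.3% | 5.1% |

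The last three columns are false-positive rates. Other runs that differed in test details gave 8.6% for test-then-drop at a total fall of 4 points, 17–19% at 8 points and 23–27% at 10 points. At 8 points the test missed the trend about 91–93% of the time. Always keeping period gave 4.8–5.3% throughout. With a continuous outcome of the same variance, test-then-drop gave 16% at 8 points and 21% at 10 points. For a 10-point step fall from period 4, test-then-drop gave 30.7% and period always kept gave 5.3%.

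**The case against.** A reader might infer that the plan drops the adjustment for time. The text does not support that. The default is a mixed model with a temporal effect assumed, the fallback is conditional and worded as a permission, and the paragraph partly surveys how stepped wedge methods depend on circumstances. The caution about within-cluster comparisons and the reproduced powers also point to an adjusted analysis.

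A reader might also take the error rates above for those of the protocol's own rule. They are not. The article specifies no test for time and no threshold, and it gives no trend. A total fall of 8 to 10 points from 26.7% is a relative fall of 30% to 37%, close to the 38% that the article treats as its smaller intervention effect. Seasonality over one year would be cyclical, so the 2.5-period factor does not describe it. The primary outcome is the rate of change in body mass and BMI, not the prevalence simulated here. With truly no trend the rule does little harm (about 6%). The authors also call the study preliminary and under-powered.

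All of this limits the size of the point. It does not remove it. A separate analysis plan might supply a criterion, but any criterion judged on these data meets the same difficulty: failing to see a trend in four wards says little about whether one exists. A permission without a criterion also leaves the choice open after the data are seen, between two analyses with visibly different standard errors.

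**Conclusion.** The point holds as a badly fixed fallback beside a sound default. That the bias is 2.5 times a linear per-period trend, and that the standard errors are 0.0495 and 0.0721, follow from the design and the article's own inputs. The false-positive rates are illustrative. Under an assumed 5% joint test, a linear fall and the binary prevalence, they run from about 6% with no trend to about 23–27% for a total fall of 10 points, against about 5% with period always kept. The direction depends on the trend: a fall in weight loss creates a false benefit, and a rise hides a real one. The documents do not establish that a trend will occur or that the fallback will be used. They do permit its use under a condition that this trial is poorly able to verify.

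**What to change.** Remove the sentence that allows the within-cluster analysis. State instead that period enters every stepped-wedge analysis as a five-level fixed categorical effect, whatever its estimate or p-value. If a within-cluster estimate without period is still wanted, present it only as a labelled sensitivity or descriptive analysis.

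The change takes one sentence. It gives up the smaller standard error (0.049 against 0.072), which is valid only if there is no trend. The stated powers of 80% and 29% stay as they are, because they were computed with period adjustment.

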### Stepped wedge trial

Though infrequently used and poorly known, awareness and use of the stepped wedge trial design is increasing [54,56-58]. Stepped wedge trials are a type of crossover trial in which different groups (or steps) cross over (ie switch from being a control to a treatment) at different time points [59]. In comparison to other crossover trials, the groups/steps only cross in one direction, from control to treatment. The first time point (Time 1) is a baseline measurement, and groups/steps are then randomised to receive the intervention at subsequent time points (Table 1) until all groups/steps have received the intervention [59]. Data is collected from all groups at regular intervals during the study, including at baseline and whenever a new group receives the intervention. At the conclusion of the trial, each of the units in each group have been exposed to the intervention, and each of the groups has a varying amount of control data collected prior to receiving the intervention (Table 1).

A stepped wedge randomised cluster trial with repeated cross section design will be employed [54,55,59]. The ‘step’ refers to each group of wards; and the ‘cluster’ refers to the ward as unit of randomisation. The ‘repeated cross section’ measures refer to the fact that multiple cross sectional measures are made with different patients in each cluster for each of the sampling time periods [55], as recently used in surgical patients across three hospitals [58].

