The stepped wedge allows all clusters to receive the intervention. Further, unlike a conventional crossover trial, no clusters are removed from the intervention, which is ethically preferable if there is the prior belief that the intervention should result in benefits for the patient population [54,55,59]. The design also allows for a staged implementation, which is particularly beneficial if there are logistical, practical or financial limitations to rolling out an intervention at all sites in one time period [59]. The design supports evidence implementation in complex, changeable environments because the staged implementation allows improvements to be made to the intervention, for example training materials can be updated to accommodate feedback from participants. Analysis of stepped wedge trials can adjust for possible temporal trends in the effectiveness of the intervention, and the design reduces the impact of intra-cluster correlations on power because each group acts as its own control [54]. A disadvantage of the design is the need for data collection from all units at each sampling period, and potential lengthening of the trial to allow sequential roll out of the intervention across all groups [54]. These attributes support the use of routinely collected hospital administrative data as outcomes of stepped wedge trials.

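### The planned mixed model names only patient and ward variance, so ward-specific change between periods is missing from the standard error; the effect is modest at the protocol's own ward SD and larger only under assumed higher variance

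*Protocol article*

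**What the plan says.** The Analysis section chooses the model in one clause: "assuming that there will be a temporal effect, linear mixed models (LMM) will be used". It then names the variance components: "Random effects will be used to model correlation between individuals within the same cluster and measure the variance of individuals in a cluster and variance", the latter meaning between wards. If time has no effect, it offers an alternative: "If there are no temporal effects, then within-cluster analysis can be used to estimate the treatment effect". Neither route names a term that lets one ward's level move between periods differently from the others.

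The power calculation rests on the same source: "Using equations seven and eight [59], a coefficient of variation". Its inputs are a prevalence of 26.7% and a ward SD of 0.056, attributed to baseline weight data from four wards, and a sample of 400 patients.

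The Stepped wedge trial section describes a repeated cross section, in which "multiple cross sectional measures are made with different patients in each cluster for each of the sampling time periods". Under Sampling, one ward per group is measured, and filling a cell of 20 patients may take a month of weekly visits. The analysis reaches widely: "All of the outcomes except for the Alberta Context Tool will be analysed according to the stepped wedge design".

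**The concern.** With a ward effect that is constant over all five periods, two patients on the same ward are equally correlated whether they were weighed in the same month or a year apart. Given ward and period, all 400 patients count as independent. Yet the 20 patients in a cell share one ward over about one month, and so may share its staffing and case mix. If that produces ward-by-period variation, it enters the cell means but not the standard error.

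Confidence intervals would then be too narrow and the test of the intervention would reject too often under the null. Four measured wards give little averaging of one ward's shift in one period. The same model serves nearly every outcome, and the Discussion says the results may inform a larger study.

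**Working it through.** **1. Reproduce the stated power.** Inputs from Analysis and Sampling: I = 4 wards, T = 5 periods, 20 patients per cell, p = 0.267, τ = 0.056. A two-sided 5% level is assumed because none is stated.

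Cell-mean variance from patients: s² = 0.267 × 0.733 / 20 = 0.009786. Ward variance: τ² = 0.003136. Design sums from Table 1 with one ward per group: U = 10, W = 30, V = 30.

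Var(θ) = I s²(s² + Tτ²) / [(IU − W)s² + (U² + ITU − TW − IV)τ²]

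= 4 × 0.009786 × 0.025466 / (10 × 0.009786 + 30 × 0.003136) = 0.00519, so SE = 0.0721.

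- 26.7% to 6.5%: Φ(0.202/0.0721 − 1.96) = 80.0% (stated 80%).
- 26.7% to 16.5%: Φ(0.102/0.0721 − 1.96) = 29.3% (stated 29%).

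Both match using patient and ward variance alone, so the stated power has no separate ward-by-period component.

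**2. Split 0.056 into stable and period-specific parts.** A between-ward SD observed at one time point already contains both. Let c be the share of ward-level variance that is stable over time (an assumption). Replace τ² by cτ² and s² by s² + (1 − c)τ².

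| c | SE | Power, 26.7% to 6.5% |
|---|---|---|
| 1 | 0.0721 | 80.0% |
| 0.8 | 0.0730 | 79.0% |
| 0.5 | 0.0737 | 78.3% |
| 0 | 0.0719 | 80.2% |

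**3. Type I error under the null.** Simulation of 4 × 5 × 20 with normal errors. The planned model (fixed periods, ward intercept, patient residual) was fitted by REML. Total ICC is ward-level variance over total variance; 0.056 gives 0.003136 / (0.003136 + 0.195711) = 0.016. The other ICCs are assumed.

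| Total ICC | c | Planned model, z | Same statistic, t on 11 df |
|---|---|---|---|
| 0.016 | 1 | about 7% | about 4.5% |
| 0.016 | 0.8 | 7.8% | 4.6% |
| 0.016 | 0.5 | 8.4% | 5.1% |
| 0.016 | 0 | 8.7% | 5.4% |
| 0.05 | 0.8 | about 9.5% | about 6% |
| 0.05 | 0.5 | about 13% | about 9% |
| 0.10 | 0.8 | about 12% | about 8% |
| 0.10 | 0.5 | about 19% | about 14% |

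Ordinary least squares on the 20 ward-period means (ward, period and intervention terms; 20 − 4 − 4 − 1 = 11 df) gave about 5% in every row.

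**4. Can the larger ICCs be excluded?** On the binary scale, ICC 0.05 means a ward SD of √(0.1957 × 0.05/0.95) = 0.10, and ICC 0.10 means √(0.1957 × 0.10/0.90) = 0.15. An SD from four wards (3 df) has 95% limits of about 0.57 to 3.7 times the estimate, ignoring patient sampling error. That is 0.056 × 0.57 = 0.032 to 0.056 × 3.7 = 0.21, so both values lie inside.

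**5. Power of the ward-period-mean analysis.** With ward as a fixed term, Var(θ) = (2/3) × (cell-mean variance).

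- No ward-by-period variance: SE = √(0.6667 × 0.009786) = 0.0808; noncentrality 0.202/0.0808 = 2.50; power on 11 df about 63%.
- Ward-by-period SD 0.056: SE = √(0.6667 × (0.009786 + 0.003136)) = 0.0928; noncentrality 2.18; power about 51%.

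**The case against.** The strongest reply concerns size. A reader might infer that the false-positive rate doubles and that true power is well below 80%. Adding a ward-by-period SD of 0.056 on top of the stated 0.056 does give about 10% type I error and about 70% power. The documents do not support that addition. The 0.056 is attributed to baseline data, a single time point, so it already includes period-specific variation. Adding the same amount again raises the ICC from 0.016 to 0.031. Taken as the total, 0.056 leaves the rate at 8-9% and the power almost unchanged. This part of the reply stands.

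It also stands that, at ICC 0.016, most of the excess comes from a z test with four wards, and that a t reference on 11 df nearly removes it. The documents name neither a z test nor degrees of freedom, so that element is assumed. At the larger assumed ICCs the t reference alone does not suffice.

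The text is thin evidence that wards do shift between periods here. The Discussion reports differences between wards in leadership, culture and feedback, which a ward effect absorbs. The remark "The design supports evidence implementation in complex, changeable environments" describes the design in general. Neither establishes ward-by-period variation in this hospital; equally, baseline data alone cannot show that it is absent.

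Finally, an article condenses a fuller plan, which might add a term. But this article does name its variance components, and the power uses exactly those two.

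**Conclusion.** The point holds as a matter of structure. The stated model and power calculation carry patient and ward variance only, and the standard error is too small whenever wards change differently between periods. This concerns precision only; nothing suggests the estimate is pushed towards or away from benefit.

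For the binary week-1 outcome, with 0.056 as the total ward-level SD, type I error is about 8-9% against a nominal 5%, of which about 7% would occur with four wards alone. The stated 80% power moves only to 78-80%. A rate of 10% or more is conditional on assumed larger variance: about 13% at ICC 0.05 with half stable, and 12% or 19% at ICC 0.10 with 80% or 50% stable. The documents give no ICC for continuous weight change or process compliance, and an SD from four wards at one time point cannot rule these values out.

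The figures assume a two-sided 5% level, a z test, normal errors and REML. The change is worth making, but the evidence does not show that the false-positive rate is doubled.

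**What to change.** In the Analysis section, add a random ward-by-period effect to the mixed model, with a small-sample reference distribution because only four wards are measured. Alternatively, for the continuous weight outcomes, analyse the 20 ward-period means with ward, period and intervention terms and a t reference on 11 df. For rare binary outcomes such as mortality, and for compliance cells near zero before the intervention introduces the tool, use a ward-period summary method suited to such data. Plain least squares on proportions would not have constant variance there.

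Restate the detectable-effect figures under the chosen analysis, with a stated range for the ward-by-period SD.

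This needs revised wording and a rerun of the power formula, with no new patients or data. The price is lower stated power: for 26.7% to 6.5% on 11 df, about 63% with no ward-by-period variance and about 51% if that SD is 0.056. The Discussion already calls the study preliminary and under-powered for all but large effects, so the lower figures fit what it says.

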### Outcomes

The primary patient outcome measure will be the rate of change in body mass and body mass index over weekly periods from admission to discharge. Body mass (kg) will be measured to the nearest 0.1 kg, between 0800 and 1200 and post bladder voiding. Depending on patient mobility this may require a standing, sitting, bed or sling weighing machine. Patient’s height (cm) will be measured to the nearest 0.1 cm using a stadiometer or predicted from measured ulna length depending on patient mobility. Body mass index (kg/m^2^) is calculated as body weight divided by height squared. The body mass data will be collected by a researcher (LL), who is not blinded to the randomisation schedule.

Secondary patient outcome measures will include: length of stay, all cause mortality, discharge destination (to a higher, lower or equivalent level of care), number and duration of re-admissions (defined as an unplanned admission within 28 days of discharge related to the primary admission [62] (3, 6, 12 months post-discharge), and number of Emergency Department (ED) presentations (3, 6, 12 months post-discharge). The re-admission and ED presentations data will be collected from across all five major public hospitals in the metropolitan region using the State’s patient record systems, which will also provide length of stay, discharge destination and mortality, cross-referenced with State death registries. The collector of the secondary patient outcome data will be blinded to the randomisation schedule.

The staff-related outcome is nurse perspectives of context of care as assessed by administration of the Alberta Context Tool (ACT) [63,64] before the intervention.

Hospital process-related outcomes include: compliance to using the MUST tool on all patients, compliance to using additional food supplements when indicated, compliance to using the red tray system when indicated and compliance to documenting patient’s foods and fluids intake by nurses. The hospital process measures will be obtained through medical record review.

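### The mixed model as described has no patient-level term; adding admission BMI would give modest, nearly free protection against patient-mix shifts that coincide with a ward's crossover

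*Protocol article*

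**What the plan says.** **Model (Analysis).** The article states that "assuming that there will be a temporal effect, linear mixed models (LMM) will be used", and then "Random effects will be used to model correlation between individuals within the same cluster". It adds a fallback: "If there are no temporal effects, then within-cluster analysis can be used to estimate the treatment effect". No patient-level covariate is named, and none is ruled out.

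**Outcome (Outcomes).** The article defines it thus: "The primary patient outcome measure will be the rate of change in body mass and body mass index over weekly periods from admission to discharge". A researcher who knows the randomisation schedule measures body mass. Height is measured, or predicted from ulna length, so BMI is available for sampled patients.

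**Patients (Stepped wedge trial; Sampling).** The design is a repeated cross-section in which "multiple cross sectional measures are made with different patients in each cluster for each of the sampling time periods". One ward per group supplies the primary data, chosen because "we will purposively sample a ward that is most likely to care for patients who have a length of stay in excess of 7 days". Within it, "patients with Diagnostic Related Groups (DRGs) known to have longer than average length of stay will be targeted". There are 20 patients per ward per period, four wards and five periods, giving 400 patients.

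**BMI in the power calculation (Analysis).** The event used there depends on BMI: a loss of at least 2 kg at BMI 20 or above, or "BMI less than 20 who lost 1 kg or more".

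**The concern.** Wards are randomised to a crossover time; patients are not randomised to a phase. From the second period on, patients enter wards whose phase is already known, and they are picked by targeting. Nothing in the allocation therefore makes a ward's intervention-phase patients resemble its control-phase patients. If the mix in a ward changes when that ward crosses over, and the changed characteristic predicts weight change, the mixed model reads part of the mix change as an intervention effect, in either direction. With one measured ward per group, few wards are available to average such shifts out.

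Admission BMI is an obvious candidate covariate. It is already collected, it is measured the same way in both phases, and the article uses BMI to decide how much loss counts as an event. The Discussion acknowledges purposive sampling as a limit on generalisability but not as a possible source of bias.

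**Working it through.** **1. Reproduce the stated power.** Inputs from Analysis and Table 1: I = 4 wards, T = 5 periods, 20 patients per cell, τ = 0.056, control prevalence 0.267. Alpha is not stated; two-sided 0.05 is assumed.

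- Cell variance: s² = 0.267 × 0.733 / 20 = 0.009786. τ² = 0.003136.
- Design sums from Table 1: U = 10 (intervention cells), W = 0 + 1 + 4 + 9 + 16 = 30 (squared period totals), V = 16 + 9 + 4 + 1 = 30 (squared ward totals).
- Closed-form stepped-wedge variance: I·s²(s² + Tτ²) / [(IU − W)s² + (U² + ITU − TW − IV)τ²] = 4 × 0.009786 × 0.025466 / (10 × 0.009786 + 30 × 0.003136) = 0.005193. SE = 0.0721.
- Power for 26.7% to 6.5%: Φ(0.202/0.0721 − 1.96) = 80.0% (stated: 80%).
- Power for 26.7% to 16.5%: Φ(0.102/0.0721 − 1.96) = 29.3% (stated: 29%).

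Both figures reproduce.

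**2. How a mix difference reaches the estimate.** The generalised least squares weights that the same model puts on the 20 cell means are:

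| Ward | P1 | P2 | P3 | P4 | P5 | Row sum |
|---|---|---|---|---|---|---|
| 1 | −0.098 | 0.300 | 0.167 | 0.035 | −0.098 | +0.31 |
| 2 | −0.033 | −0.165 | 0.233 | 0.100 | −0.033 | +0.10 |
| 3 | 0.033 | −0.100 | −0.233 | 0.165 | 0.033 | −0.10 |
| 4 | 0.098 | −0.035 | −0.167 | −0.300 | 0.098 | −0.31 |

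- Each column sums to zero, so a mix change common to all wards in a period cancels exactly.
- Row sums are not zero, so stable ward differences are only partly removed.
- The weights on intervention cells sum to 1, so a shift that starts in each ward at its own crossover passes through in full.

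**3. Size of an aligned shift (assumed values).** Bias = shift in SD units × covariate-outcome correlation × outcome SD, with outcome SD = √(0.267 × 0.733) = 0.442.

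- Smallest case: 0.1 × 0.1 × 44.2 = 0.4 percentage points.
- Largest case: 0.5 × 0.3 × 44.2 = 6.6 percentage points.

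The SE is 7.2 points and the article's smaller effect is 26.7 − 16.5 = 10.2 points. The article gives no evidence on whether such a shift will occur, or how large it would be.

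**4. Chance imbalance.** The sum of squared weights is 0.464, so chance imbalance in any patient covariate has an SD of √(0.464/20) = 0.152 covariate SDs in the effect contrast. As an illustration, assume weight-loss prevalence of 40% below BMI 20 and 23% otherwise. The share below BMI 20 that gives 26.7% overall is (0.267 − 0.23)/0.17 = 21.8%. Chance imbalance in that share then has an SD of 0.152 × √(0.218 × 0.782) = 6.3 points, which is 6.3 × 0.17 = 1.1 points of prevalence. This is random error already contained in the 7.2-point SE.

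**5. Power after adjustment.** Multiply s² by (1 − ρ²) and repeat step 1:

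| ρ (assumed) | 26.7% to 6.5% | 26.7% to 16.5% |
|---|---|---|
| 0 | 80.0% | 29.3% |
| 0.1 | 80.4% | 29.5% |
| 0.2 | 81.4% | 30.2% |
| 0.3 | 83.2% | 31.4% |

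The 40%/23% illustration implies ρ = 0.17 × 0.413 / 0.442 = 0.16, which gives 80.9% and 29.9%.

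Steps 3 to 5 use the binary prevalence measure because it is the only one for which the article gives a variance. The primary outcome is continuous change, so these figures indicate scale only.

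**The case against.** The strongest objection is that this rests on silence. The article is condensed, and a covariate list commonly sits in a full protocol or analysis plan that is not shown. A reader might infer that the primary model adjusts only for time and ward; the article does not say so. That stands, and it is why this is a suggestion and not an error.

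A reader might also infer that any difference in patient mix between phases goes straight into the effect. The planned model does not behave that way. Shared changes cancel, stable ward differences are partly removed, and the outcome is already a change from admission. Nor is chance imbalance in cells of 20 confounding, since the SE already carries it.

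The BMI-dependent thresholds define what counts as a loss; they do not show that mean weight change depends on BMI. The Background's remark on greater benefit in underweight patients concerns mortality, morbidity and function, so it does not show confounding of weight change either.

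Finally, BMI would not correct selection on illness severity or diagnosis group. That also stands.

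What survives is narrower. The sampling leaves a route for ward-specific shifts aligned with crossover, the described model does nothing specific about it, and a suitable covariate is already in hand. The fallback widens the route: without period effects, a within-ward before-after comparison also absorbs hospital-wide mix changes.

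**Conclusion.** The point holds as a small, nearly free improvement. The model described has no patient-level term. A mix shift that is specific to a ward and coincides with its crossover can bias the estimate, by about 0.4 to 6.6 percentage points of prevalence over the assumed range of shifts (0.1 to 0.5 SD) and correlations (0.1 to 0.3). Whether such shifts will arise cannot be judged from the article. The precision gain is modest: at most 3.2 points of power at the larger effect (80.0% to 83.2%) and 2.1 points at the smaller (29.3% to 31.4%) for correlations up to 0.3. Adjustment corrects only the part of selection that admission BMI captures. These sizes rest on an assumed two-sided 5% level, assumed correlations, and the binary measure standing in for continuous change.

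**What to change.** State in Analysis that the primary linear mixed model for weekly change in body mass, and the one for change in BMI, each contain fixed effects for period and intervention, the ward random effect, and the patient's admission BMI as a prespecified covariate. Take BMI from the researcher's measurements and not from the ward's MUST score, because the intervention itself introduces MUST scoring. Carry the same covariate into the within-cluster analysis if that fallback is used. Report the unadjusted model as a sensitivity analysis.

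The cost is a sentence or two of text and one extra parameter per model with 400 patients. No new data or visits are needed.
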